## Data collection and management

This trial will be centrally coordinated from the Trial Coordination Center (TCC) at the Indian Institute of Public Health (IIPH) Hyderabad. Baseline data will be collected by the investigator and follow-up data will be collected with appropriate translation by an independent blinded outcome assessor on paper forms. These data will be securely scanned and sent to the TCC for entry into the password-protected, secured electronic database. An independent data safety and monitoring committee (DSMC) will be set up to monitor data collection and management. A trial steering committee will also be set up to oversee the conduct of the trial.

## Analysis

The main analyses will compare all those allocated to the ‘Care for Stroke’ intervention with those allocated to the standard treatment group on an ‘intention-to-treat’ basis, irrespective of whether the participants received the treatment allocated or not. The imbalance in recruiting equal number of participants if any will be addressed during the analysis phase using appropriate statistical techniques. The dichotomised MRS scores (0–3 and 4–6) in both the groups will be used to calculate the effect estimates with a measure of precision (95% CI) and presented in the results of the trial. Subgroup analysis for the primary outcome will be based on stroke severity, location of the participant (urban/rural), gender and age at stroke. Interaction tests will also be used to test whether the effect of treatment (if any) differs across these subgroups.

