## Eligible participants

### Inclusion criteria

Adults (aged ≥18 years).Recent diagnosis of first ever stroke as defined by the WHO.^21^Any level of stroke severity (score 1–42, according to National Institute of Health (NIH) stroke scale.^22 23^)Stroke survivor medically stable (reaching a point in medical treatment where life-threatening problems following stroke have been brought under control).Poststroke functional status of the stroke survivor: requiring assistance of at least one person to perform daily activities such as transfers, self-care and mobility (ie, scoring less than the maximum score obtainable in one or more components of the Barthel Index^24^).Stroke survivor residing with a primary caregiver (family member) at home.

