## Randomisation

Stroke survivors will receive all-usual treatment for stroke. Participants eligible for inclusion will be identified by a trial investigator. The eligible participants will be initially contacted by telephone and they will be visited in person at their home by the investigator to share the details about the study to the participant and the identified caregiver. A participant information sheet outlining the study objectives, risks and benefits along with brief information sheet about stroke will be provided to the participant. Written informed consent for participation in the intervention will be sought from all participants or from the next of kin if the participant is unable to consent.

An entry form will be used to collect baseline information including the contact details of the participant and the identified caregiver. This information will be forwarded to the independent randomisation centre and the participants eligible for inclusion will be randomised to the intervention or control arm in a 1:1 ratio using a secure, central, password-protected, web-based system. The intervention will be started within 24 hours of randomisation.

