## Outcome measures

### Primary outcome

The primary outcome measure is dependency in activities of daily living and will be measured by the MRS^27^ at baseline and at 6 weeks after randomisation. The MRS scale measures the degree of disability or dependence in the activities of daily living of people who have suffered a stroke in six categories. The scores range from 0 (no symptoms) to a maximum of 6 (dead). A dichotomous approach to outcome analysis will be used. Participants’ scores will be categorised into MRS scores of 0–3 and 4–6.

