## Follow-up

An outcome form will be completed at 6 weeks after randomisation or at death, if either happens sooner. A blinded outcome assessor will evaluate all the outcomes (primary and secondary) at baseline and at 6 weeks. A relatively short follow-up period has been selected as The Stroke Therapy Academic Industry Round Table strongly recommends a shorter follow-up period to reduce variation in clinical outcome that could occur due to subsequent stroke events that are unrelated to the trial.^24^ This will also allow accurate assessment of the outcome.^30^

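### The Analysis section promises a correction for unequal arm sizes, which none is needed for, and states no use of the baseline MRS, which would add precision

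*Protocol article*

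**What the plan says.** Under Analysis, the article plans an intention-to-treat comparison of the two arms. It then adds: "The imbalance in recruiting equal number of participants if any will be addressed during the analysis phase using appropriate statistical techniques". The dichotomised MRS scores "in both the groups will be used to calculate the effect estimates with a measure of precision (95% CI"). No model, effect measure or covariate is named. Baseline variables (severity, urban or rural location, gender, age) appear only as subgroup factors with interaction tests.

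Under Primary outcome, MRS is measured "at baseline and at 6 weeks after randomisation", and "Participants’ scores will be categorised into MRS scores of 0–3 and 4–6". Under Randomisation, participants are "randomised to the intervention or control arm in a 1:1 ratio using a secure, central, password-protected, web-based system". Inclusion criteria admit NIHSS 1 to 42 and anyone needing help in daily activities, defined as "scoring less than the maximum score obtainable in one or more components of the Barthel Index". No entry criterion is set in terms of MRS.

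On who scores MRS at baseline, Follow-up says: "A blinded outcome assessor will evaluate all the outcomes (primary and secondary) at baseline and at 6 weeks". Data collection and management says: "Baseline data will be collected by the investigator and follow-up data will be collected with appropriate translation by an independent blinded outcome assessor".

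**The concern.** The one imbalance that the Analysis section undertakes to deal with is imbalance in numbers. Under randomisation that needs no remedy. A technique chosen in the analysis phase leaves the primary comparison open to choices made after the data are seen.

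The imbalance that can move an estimate by chance is prognostic. With such wide entry criteria, participants may differ greatly in dependency at entry, and the 6-week category may partly reflect where each person began. The trial collects the obvious covariate, the same scale at baseline, and the article states no use for it in the primary comparison. What is at stake is precision and power.

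If baseline MRS is to serve as a covariate, it must also be clear who scores it and that this happens before allocation. Two sections of the article disagree on the role.

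**Working it through.** **Number of evaluable participants.** Inputs from Sample size estimation: 50% event rate, a 20% difference (read as 20 percentage points), 90% power, 5% one-sided, 20% loss. The non-inferiority formula with 50% in both arms gives

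n = 2 × 0.5 × 0.5 × (1.645 + 1.282)² / 0.20² = 107.05 per arm; 107.05 / 0.8 = 133.8; total 267.6.

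Rounding up at each step gives 108, then 135 per arm, or 270 in total. Either is close to the stated 266. Working back, 133 × 0.8 = 106.4, so about 106 per arm are evaluable. The sample size is not in dispute here.

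**Unequal arms: precision.** With equal outcome variance in the arms, the variance of the difference is proportional to 1/n₁ + 1/n₀. The ratio to an even split is (1/n₁ + 1/n₀) / (4/266):

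| Split | Variance ratio | Power, 50% v 30%, two-sided 5%, no dropout |
|---|---|---|
| 133 / 133 | 1.000 | 91.9% |
| 140 / 126 | 1.003 | 91.8% |
| 146 / 120 | 1.010 | 91.6% |
| 160 / 106 | 1.043 | 90.7% |

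Under simple randomisation (an assumption; the article names no scheme beyond 1:1), a split at least as uneven as 146 v 120 has probability about 12.5%.

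**Unequal arms: bias.** In simulations with 212 evaluable and a true difference of −0.20, the mean estimate was −0.200 to −0.202 at both 106/106 and 127/85. There is nothing to correct.

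**Unadjusted power at the stated one-sided 5%, 106 per arm.** Here the 20 points are treated as a difference to detect.

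Power = Φ{[d − 1.645 √(2p̄(1−p̄)/n)] / √([p₁(1−p₁) + p₀(1−p₀)]/n)}

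- 50% v 30%: p̄ = 0.40. (0.20 − 1.645 × 0.0673) / 0.0659 = 1.36, so power is 91.2%.
- 50% v 35%: p̄ = 0.425. (0.15 − 1.645 × 0.0679) / 0.0671 = 0.57, so power is 71.6%.

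**Adjusted power.** The article gives no link between baseline and 6-week MRS, so it has to be assumed. The simulation used correlated latent normal scores at the two times and logistic regression on arm and baseline MRS, with the same one-sided 5% test:

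| Scenario | Unadjusted | Adjusted, latent correlation 0 to 0.7 |
|---|---|---|
| 50% v 30% | about 91% | about 91% to 96% |
| 50% v 35% | about 72% | about 72% to 85% |

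A repeat run with baseline grades 1 to 5 set at 3, 10, 22, 40 and 25% (also an assumption) agreed to within about 2 percentage points. At correlation 0 there is no gain.

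**Baseline scoring.** Follow-up gives all outcomes at baseline to a blinded assessor. Data collection and management gives baseline data to the investigator and only follow-up data to the blinded assessor. Primary outcome makes MRS a baseline measure, so both cannot hold for it.

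**The case against.** A reader might infer that the primary comparison is fixed as unadjusted. The article does not say so. It is silent on model and covariates, and an article may leave those to the full protocol or the analysis plan, neither of which is shown. That objection stands: the absence of a named covariate is not in itself an error.

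A reader might also infer that the result would be biased. It would not. An unadjusted intention-to-treat contrast is valid under randomisation, and its confidence interval already allows for chance imbalance.

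Nor do the documents show that arms would be weighted or trimmed to equal size. The planned technique might be no more than a standard error that uses the actual numbers. The step is announced in advance, and only its method is open, so calling it post hoc would fit only the choice of method. The sentence may also have been meant for baseline characteristics.

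On size, a two-sided 5% test would start from 84.9% (50% v 30%) and 59.9% (50% v 35%) and leave more room for gain. Sample size estimation states one-sided 5%, so those larger gains do not describe the design as written.

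Finally, the disagreement on baseline scoring is a side point. Randomisation has baseline information collected on an entry form before allocation, so for anything scored at that stage the assessor's blinding to allocation is not at risk.

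What survives is the sentence itself. It is stated text, not an omission; as written it addresses a non-problem and leaves the remedy open. If baseline imbalance was meant, it says something else and names no covariate. Either way it needs changing.

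**Conclusion.** The point holds in a limited form. The correction for unequal numbers is unnecessary: a 146 v 120 split costs about 1.0% in variance, a 160 v 106 split about 4.3%, and neither causes bias. Replacing it with pre-specified adjustment for baseline MRS is a better use of data that the trial already collects.

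The benefit is precision only. At one-sided 5% with 106 per arm it is worth 0 to about 5 percentage points of power for 50% v 30% (96 − 91) and 0 to about 13 for 50% v 35% (85 − 72). These figures rest on an assumed latent correlation of 0 to 0.7 and an assumed baseline distribution. They vanish if baseline MRS is not prognostic, which is unlikely for the same scale scored six weeks apart.

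Separately, Follow-up and Data collection and management contradict each other on who scores the baseline outcomes.

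**What to change.** 1. Delete the sentence on unequal numbers. If prognostic imbalance was meant, say that instead and name the covariates in advance.
2. State that the primary comparison of MRS 0–3 v 4–6 adjusts for baseline MRS. Age and NIHSS score are further candidates, since severity and age are already subgroup factors.
3. Report a standardised risk difference: average the model's predicted risk of MRS 4–6 over all analysed participants under each allocation, and subtract. A logistic coefficient alone gives a conditional odds ratio, which does not match the 20% difference used for the sample size. Give the unadjusted difference as supportive.
4. Reconcile Follow-up with Data collection and management so that one named role scores baseline MRS in both arms, before randomisation.

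Items 1 to 3 are wording only: the data are already planned and 266 is unaffected. Item 4 is also wording, unless the role chosen differs from current practice in the field.

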### Recruitment of participants

The trial will identify and recruit participants from the hospital records as well as stroke insurance records available at the Aarogyasri trust until the sample size is achieved. Currently, the average stroke insurance claim rate through this trust is 10–12 stroke survivors per month. Hence, it would take approximately 32–36 months for recruiting the proposed number of participants in this trial.

## Patient and public involvement

Patients and public were not involved for the purpose of protocol development.
